### Eligibility criteria

Patients aged ≥18 years with a diagnosis of EC will be eligible for study inclusion. Expanded inclusion criteria will be used as not all patients with suspected EC undergo diagnostic biopsies due to the costs associated with biopsy and pathological review. Diagnostic criteria for EC will include either histopathological confirmation or clinical diagnosis based on barium swallow (esophagram) and/or upper endoscopy without biopsy. This clinical criteria has been shown to have a > 90% pre-test probability for the diagnosis of ESCC in Eastern Africa [17]. Access to a mobile phone is not a requirement for study entry; however, should a study participant lack access, this will be noted on baseline enrollment forms. Patients who have previously received treatment for EC will be eligible for study participation; in these cases, details of prior EC treatment will be abstracted from medical records, if available.

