**Overall well-being** Which of the following best describes your quality of life now as compared to before you were treated for esophageal cancer?	“A lot better”	“A little better”	“The same”	“A little worse”	“A lot worse”

^a^Modified quality of life index reprinted with permission from Rosenblatt (2010, Table 1)

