### Recruitment and consent of study participants

Patients who present to participating AfrECC sites with symptoms concerning for or a new diagnosis of EC will be identified by the research team. Since many patients with ESCC are ill and subject to clinical deterioration, we will employ rapid case ascertainment strategies to identify all cases of EC seen for further care. Study teams are embedded in clinical care settings. At designated times each week, research coordinators will use the following strategies to identify eligible patients with suspected diagnoses of ESCC: 1) contact physicians caring for inpatients on both medical and surgical wards and review current ward rosters; 2) review the schedule of endoscopy cases to be performed, including diagnostic and therapeutic procedures (if applicable); 3) review pathology reports (if applicable); 4) contact clinicians seeing patients in the outpatient setting; and 5) review chemotherapy and radiation schedules to identify patients with plans to undergo ESCC treatment (if applicable).

Once potential study participants are identified, they will be approached by a research assistant to assess eligibility and willingness to participate in this study. Study participants will be thoroughly informed about all aspects of the study, including study follow up plans and all regulatory requirements for informed consent. Written informed consent will be obtained prior to study enrollment. The informed consent documents will be available in both English and the local language(s) at each site. Study participants will receive a phone card as a small token of compensation for participation, valued at 5 USD in Kenya and Tanzania and 10 USD in Malawi, in accordance with the local institutional standards.

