### Data collection procedures

#### Case report forms (CRFs)

CRFs are comprised of both medical chart abstraction instruments and standardized questionnaires. CRFs collect socio-demographic details (including age, sex, ethnicity, location of permanent residence, highest level of education completed, self-reported annual household income, health insurance status), baseline clinical information, treatment-related data, as well as vital status and QOL metrics over long-term follow up (see Table 3).

**Table 3 Tab3:** Data collected during TOEC-Eastern Africa study

Collected data	Baseline	Prior to treatment	During treatment	Follow up^**a**^
Sociodemographic				
Age	x			
Sex	x			
Ethnicity	x			
Occupation	x			
Location of permanent residence	x			
Highest level of education completed	x			
Annual household income	x			
Health insurance status	x			
Smoking and alcohol use	x			
Clinical data				
Medical History	x			
HIV status (date of and last CD4 count, use of antiretrovirals)	x			
Date/method of diagnosis	x			
Histopathological data (if applicable)	x			
Endoscopic findings (location/length of tumor)	x			
Imaging (if applicable)^b^	x			
Use of opiate medications for pain control	x	x		x
Hospitalizations			x	x
Vital status (including cause of death, if applicable)			x	x
Treatment				
Prior EC treatment (if applicable)	x			
EC treatment received, including delays/interruptions in treatment and reasons			x	
Complications			x	
Response assessment (if applicable)			x	
Quality of life				
Modified Rosenblatt Index^c^	x	x		x

*EC* Esophageal cancer

^a^Follow up assessments performed 1 month after initiation of treatment, 3 months after initiation of treatment, and then every 3 months until death or loss to follow up

^b^Any imaging modality performed during baseline assessment, including chest x-ray, ultrasound, computed tomography, positron emissions tomography, etc.

^c^The Modified Rosenblatt Index assesses the following: Dysphagia, Odynophagia, ‘Chest and/or Back pain,’ WHO performance status, and ‘Overall Well-being’ since starting treatment

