OS will be defined in two ways: 1) from the date of initial diagnosis to the date of death or last patient contact; and 2) from date of initiation of treatment to date of death or the date of last patient contact. Kaplan-Meier method will be used to summarize OS and log-rank test will be used to compare survival curves among treatments overall and stratified by the study center. Furthermore, Cox proportional hazards (cph) modeling will be used to account for demographic and clinicopathological factors by including them as covariates. Proportionality of hazards for key covariates will be tested by examining the correlation between time and scaled Schoenfeld residuals and log-log plots of survival. Important covariates that violate the proportionality assumption will be used to stratify the cph model. In many settings in Eastern Africa, long delays can occur between diagnosis and initiation of treatment. To mitigate immortal time bias that can emerge in time-to-event analyses of observational studies, two analytical approaches will be employed. First, in analyses using OS defined by date of diagnosis, the time from diagnosis to the initial treatment will be added as a covariate. Secondly, in analyses of associations between different treatments and OS, treatment status will be included in Cox regression modeling as a time-varying covariate (defined as treated versus untreated). This approach allows for patients to accrue follow up time while awaiting treatment, while also accounting for any events that occur during the ‘untreated’ waiting period [20]. Our primary analysis will examine pairwise comparisons of: stenting vs. radiotherapy with or without chemotherapy, stenting vs. chemotherapy, and radiotherapy with or without chemotherapy vs. chemotherapy. Among patients receiving radiation, outcomes may differ between patients receiving radiotherapy alone as compared to concurrent chemoradiation. Exploratory analyses will examine these subgroups separately.

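### The primary survival contrasts pool first-line and later-line treatment, with no rule for which treatment sets a previously treated patient's group and clock; separately, the well-being item has no usable baseline

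*Protocol article*

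**What the plan says.** All references are to the protocol article, Methods.

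- **Eligibility criteria.** "Patients who have previously received treatment for EC will be eligible for study participation". No limit is set on type, number or timing of earlier treatment. For these patients "details of prior EC treatment will be abstracted from medical records, if available". Table 3 lists prior treatment as a baseline field.
- **Recruitment and consent.** "Patients who present to participating AfrECC sites with symptoms concerning for or a new diagnosis of EC will be identified by the research team". The same paragraph says that the aim is to "identify all cases of EC seen for further care".
- **Statistical methods, population.** All consenting patients with a histological or clinical diagnosis are analysed.
- **Statistical methods, OS.** The three primary pairwise contrasts are stenting, radiotherapy with or without chemotherapy, and chemotherapy against each other. OS is measured from initial diagnosis (the definition under Primary endpoint) and also from initiation of treatment. For the diagnosis-based version, "the time from diagnosis to the initial treatment will be added as a covariate". Treatment also enters a Cox model as a time-varying treated/untreated indicator. Adjustment is for demographic and clinicopathological factors; prior treatment is not named.
- **Quality of life (QOL).** The Overall well-being item in Table 2 reads "Which of the following best describes your quality of life now as compared to before you were treated for esophageal cancer". Table 3 schedules the index at baseline, before treatment and at follow-up. Statistical methods lists the item among the index metrics and tests within-subject change in scores from baseline or pre-treatment.

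**The concern.** A modality contrast can be interpreted only if each patient's treatment and time zero are unambiguous and the groups are at a comparable point in the disease. Admitting previously treated patients suits the descriptive aims. Carrying them unseparated into the primary contrasts mixes the effect of a first treatment with that of a treatment given after an earlier one.

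The document gives reasons to expect sequential treatment. In Table 1, the Ocean Road site has external beam radiotherapy but no stents, the Muhimbili site has stents but no radiotherapy, and the Kilimanjaro site refers radiotherapy to Ocean Road. The fourth objective studies later intervention for recurrent or persistent dysphagia. If previously treated patients collect in one group and differ in prognosis, part of the observed difference is case mix.

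The well-being item is a separate problem. A question about change since before treatment cannot supply the starting value for a change score.

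**Working it through.** **1. One patient, several readings.** Take a patient who had chemoradiation before enrolment and is stented on study.

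| Element of the plan | If the earlier treatment counts | If the on-study treatment counts |
|---|---|---|
| Group in the primary contrasts | Radiotherapy with or without chemotherapy | Stenting |
| Initial treatment in the delay covariate | Chemoradiation | Stent |
| Start of the treatment-based OS clock | Before enrolment | After enrolment |
| Treated/untreated indicator at enrolment | Treated | Untreated until stented |

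The text chooses neither column, and nothing prevents a mixture, such as a stenting group with chemoradiation as the initial treatment.

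**2. Survival to enrolment.** With OS from initial diagnosis, a patient who was diagnosed, treated and only later enrolled could not have died before enrolment and still be in the data. The delay covariate describes diagnosis to treatment, and the indicator describes treated versus untreated time. Neither removes the interval from diagnosis to enrolment from the risk set.

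**3. Size of the case-mix effect (illustration; all inputs assumed).** Let a share f of a group be previously treated with k times the hazard, and let the true treatment hazard ratio be 1. At time zero:

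HR(stent/RT) = (1 − f_S + f_S·k) / (1 − f_R + f_R·k)

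Medians solve (1 − f)·2^(−t/27) + f·2^(−k·t/27) = 0.5, with an untreated-before-enrolment median of 27 weeks in both groups.

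| k | f_S | f_R | Initial HR | Medians, weeks (stent, RT) |
|---|---|---|---|---|
| 1.5 | 0.30 | 0.10 | 1.15/1.05 = 1.10 | 23.8, 25.9 |
| 2.0 | 0.30 | 0.10 | 1.30/1.10 = 1.18 | 21.7, 25.1 |
| 1.5 or 2.0 | 0.30 | 0.30 | 1.00 | equal |

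The distortion comes from unequal shares, not from pooling as such.

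**4. The plan's power, then power after restriction.** Inputs from Sample size: 1102 stented; 464 + 212 = 676 radiotherapy with or without chemotherapy; 145 chemotherapy; medians 36, 27 and 14 weeks; alpha 0.0167. Assumed: exponential survival, two-sided test, uniform accrual over about 200 weeks (47 months), and 26 weeks' minimum follow-up.

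- Event probability = 1 − [e^(−26λ) − e^(−226λ)] / (200λ), with λ = ln 2 / median. Stenting and radiotherapy together give about 1541 events.
- Schoenfeld power = Φ( √(D·p·(1−p))·|ln HR| − z ), with D = 1541, p = 1102/1778 = 0.620, HR = 27/36 = 0.75 and z = 2.39. This is Φ(5.48 − 2.39) = 0.999. With 14 months' accrual (1210 events) it is 0.993. The stated 0.99 is reproduced, as are the two stated values of 1.00.

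Excluding an assumed equal share of every group:

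| Excluded | Events | Power, stenting vs radiotherapy |
|---|---|---|
| 10% | 1387 | 0.998 |
| 20% | 1233 | 0.994 |
| 30% | 1079 | 0.986 |
| 50% | 771 | 0.931 |

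Stenting versus chemotherapy stays at 1.00, and radiotherapy versus chemotherapy stays at or above 0.993.

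**5. QOL items in Table 2.** Dysphagia, odynophagia, regurgitation, chest-back pain and performance status ask about the current state. Only Overall well-being refers back to a time before treatment. At baseline an untreated patient has nothing to compare with, and a previously treated patient answers about the earlier treatment.

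**The case against.** **Recruitment.** A reader might infer that Eligibility contradicts Recruitment, because the latter mentions new diagnoses. It does not. Recruitment covers concerning symptoms or a new diagnosis, aims at all cases seen for further care, and screens therapeutic endoscopy lists and chemotherapy and radiation schedules. Previously treated patients fit that description.

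**QOL.** A reader might also infer that the whole QOL baseline is spoiled. Five of the six items have valid current-state baselines, so the dysphagia endpoints do not share this wording problem. The well-being defect exists for untreated patients whatever the eligibility rule says, so excluding previously treated patients would not cure it.

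**Size.** It is tempting to put a large figure on the bias. If 20% of the stenting group were previously treated with half the survival, its median would fall from 36 to 31.1 weeks, 54% of the planned 9-week gap to radiotherapy. That places all such patients in one group, on an assumed prognosis and the treatment-start clock. The same share in both groups gives 31.1 and 23.3 weeks, a ratio still of 0.75. On the diagnosis-based primary clock, guaranteed survival to enrolment can act in the opposite direction.

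**Detail left to an analysis plan.** Prior treatment is collected, Cox adjustment is planned, and a covariate list is commonly left to an analysis plan. That stands for the list. It does not answer the rules the article does state: everyone is analysed, the contrasts are by modality only, and the treatment variables do not separate earlier from on-study treatment.

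**Conclusion.** The point holds in this form. Pooling treatment lines, without a rule for the index treatment, leaves the group and time zero undefined for previously treated patients in the primary analysis, and survival to enrolment is unhandled on the primary clock. This is a problem of definition and possible bias, not of power.

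Its size and direction cannot be determined: the share of previously treated patients, their spread across groups and their prognosis are not stated. The initial hazard ratios of 1.10 to 1.18 rest wholly on assumed inputs and vanish with equal shares.

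The well-being point is separate and narrower. It affects one item and its within-subject test, and it follows directly from the item's wording and schedule.

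**What to change.** In Statistical methods, OS paragraph:

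- Define the index treatment, and time zero for the treatment-based clock, as the first on-study treatment.
- Make patients with no esophageal cancer treatment before enrolment the population for the three primary OS contrasts. Keep the pooled set as a sensitivity analysis stratified by prior treatment (none, any, unknown).
- For OS from diagnosis, let patients enter the risk set at enrolment (delayed entry).

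In the QOL paragraph, drop Overall well-being from the within-subject test against baseline and compare it only between groups after treatment. The other items stay as planned.

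Eligibility need not change; the descriptive aims keep all patients.

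**Cost.** This is mainly analysis wording, since prior treatment is already a baseline field. The primary contrasts lose some patients, with the power shown above. Because prior treatment is abstracted only where records exist, some misclassification will remain, hence the unknown stratum. Referral between sites leaves a residual dependence on where a patient is first enrolled: someone stented at Muhimbili counts as untreated before enrolment if enrolled there first, but as previously treated if first enrolled at Ocean Road. This should be acknowledged when results are reported.

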### Recruitment and consent of study participants

Patients who present to participating AfrECC sites with symptoms concerning for or a new diagnosis of EC will be identified by the research team. Since many patients with ESCC are ill and subject to clinical deterioration, we will employ rapid case ascertainment strategies to identify all cases of EC seen for further care. Study teams are embedded in clinical care settings. At designated times each week, research coordinators will use the following strategies to identify eligible patients with suspected diagnoses of ESCC: 1) contact physicians caring for inpatients on both medical and surgical wards and review current ward rosters; 2) review the schedule of endoscopy cases to be performed, including diagnostic and therapeutic procedures (if applicable); 3) review pathology reports (if applicable); 4) contact clinicians seeing patients in the outpatient setting; and 5) review chemotherapy and radiation schedules to identify patients with plans to undergo ESCC treatment (if applicable).

Once potential study participants are identified, they will be approached by a research assistant to assess eligibility and willingness to participate in this study. Study participants will be thoroughly informed about all aspects of the study, including study follow up plans and all regulatory requirements for informed consent. Written informed consent will be obtained prior to study enrollment. The informed consent documents will be available in both English and the local language(s) at each site. Study participants will receive a phone card as a small token of compensation for participation, valued at 5 USD in Kenya and Tanzania and 10 USD in Malawi, in accordance with the local institutional standards.

### Data collection procedures

#### Case report forms (CRFs)

CRFs are comprised of both medical chart abstraction instruments and standardized questionnaires. CRFs collect socio-demographic details (including age, sex, ethnicity, location of permanent residence, highest level of education completed, self-reported annual household income, health insurance status), baseline clinical information, treatment-related data, as well as vital status and QOL metrics over long-term follow up (see Table 3).

**Table 3 Tab3:** Data collected during TOEC-Eastern Africa study

Collected data	Baseline	Prior to treatment	During treatment	Follow up^**a**^
Sociodemographic				
Age	x			
Sex	x			
Ethnicity	x			
Occupation	x			
Location of permanent residence	x			
Highest level of education completed	x			
Annual household income	x			
Health insurance status	x			
Smoking and alcohol use	x			
Clinical data				
Medical History	x			
HIV status (date of and last CD4 count, use of antiretrovirals)	x			
Date/method of diagnosis	x			
Histopathological data (if applicable)	x			
Endoscopic findings (location/length of tumor)	x			
Imaging (if applicable)^b^	x			
Use of opiate medications for pain control	x	x		x
Hospitalizations			x	x
Vital status (including cause of death, if applicable)			x	x
Treatment				
Prior EC treatment (if applicable)	x			
EC treatment received, including delays/interruptions in treatment and reasons			x	
Complications			x	
Response assessment (if applicable)			x	
Quality of life				
Modified Rosenblatt Index^c^	x	x		x

*EC* Esophageal cancer

^a^Follow up assessments performed 1 month after initiation of treatment, 3 months after initiation of treatment, and then every 3 months until death or loss to follow up

^b^Any imaging modality performed during baseline assessment, including chest x-ray, ultrasound, computed tomography, positron emissions tomography, etc.

^c^The Modified Rosenblatt Index assesses the following: Dysphagia, Odynophagia, ‘Chest and/or Back pain,’ WHO performance status, and ‘Overall Well-being’ since starting treatment

#### Patient interviews

Interviews with study participants will be conducted at the following specified time-points: (i) at time of study enrollment); (ii) prior to the initiation of treatment (within 4 weeks); and (iii) during post-treatment follow up (1 month after initiation of treatment, 3 months after initiation of treatment, and then every 3 months until death or loss to follow up). Research assistants will collect data on sociodemographic characteristics, medical history, and baseline QOL through face-to-face administration of oral questionnaires at the time of study enrollment. QOL assessments are based on the ‘Modified Rosenblatt Index,’ [16] a questionnaire comprised of six patient-reported outcomes assessing for the presence and severity of the following as scored on a Likert scale: Odynophagia, Dysphagia, ‘Chest and/or Back pain,’ WHO performance status, and ‘Overall Well-being’ since starting treatment (see Table 2). Subsequent interviews assessing vital status and QOL will be performed through mobile phone outreach. During post-treatment follow up, research assistants will attempt to contact patients a minimum of three times over the follow up interval before patients are classified as “lost to follow up.” Outreach attempts will be made at varying times of the day on three different days of the week.

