### Study design

This study is designed as a multi-center, prospective, observational, open cohort study. Initiation of recruitment has been staggered across sites, with the earliest commencing in February 2019 and additional sites beginning recruitment in 2021. Enrollment is scheduled to complete in December 2022, with follow-up to complete in June 2023. In total, approximately 2476 patients are expected to be enrolled in the study. Patients will be followed to collect key clinical and treatment-related data including overall survival and QOL metrics until death or loss to follow up. QOL metrics will be assessed at the time of study enrollment, prior to the initiation of treatment, and during post-treatment follow up (1 month after initiation of treatment, 3 months after initiation of treatment, and then every 3 months until death or loss to follow up). The accrual period is expected to range between 22 and 47 months across sites. Duration of follow up will differ by site due to the staggered initiation of recruitment, however, study participants will be followed for at least 6 months and up to a total of 53 months.

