#### Chart abstraction

Clinical information will be abstracted from the patient’s medical record at baseline (at time of study enrollment), during treatment(s), and following completion of any treatment(s). Clinical and treatment data collected through chart abstraction is summarized in Table 3. Treatment data will include dates of treatment, procedural details (stenting, esophagectomy, gastrostomy tube placement), radiation treatment regimens, chemotherapy regimens, major treatment- and disease-related complications, best response to treatment (if evaluated), reasons for discontinuing treatment or pursuing supportive care, and date and cause of death. Data will be collected on the time elapsed from diagnosis to initiation of treatment to account for any treatment delays that may explain differences in survival during analyses.

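### Phone-based vital-status follow-up that stops at loss to follow-up can leave deaths unlearned and informatively censored, overstating OS and, if ascertainment differs by site, biasing the treatment comparison

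*Protocol article*

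**What the plan says.** - **Source of vital status.** Patient interviews: "Subsequent interviews assessing vital status and QOL will be performed through mobile phone outreach". The abstract says the same.
- **Phone access.** Eligibility criteria: "Access to a mobile phone is not a requirement for study entry; however, should a study participant lack access, this will be noted" on the baseline form. No alternative contact route is given for these patients.
- **Loss rule.** Patient interviews: "research assistants will attempt to contact patients a minimum of three times over the follow up interval before patients are classified as" lost to follow-up. Attempts are spread over different times of day and three different weekdays.
- **End of follow-up.** Study design: "Patients will be followed to collect key clinical and treatment-related data including overall survival and QOL metrics until death or loss to follow up". Patient interviews and the Table 3 footnote end follow-up at the same point.
- **Censoring.** Statistical methods defines OS "from the date of initial diagnosis to the date of death or last patient contact", with a second definition starting at treatment initiation. Primary endpoint is to the same effect.
- **Second source of deaths.** Chart abstraction lists "reasons for discontinuing treatment or pursuing supportive care, and date and cause of death" among the items taken from the record, and Table 3 lists vital status, with cause of death, during treatment and at follow-up.

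**The concern.** A patient who has died cannot answer the phone. If nobody else reports the death and it is not in the chart, the patient may be classed as lost and OS is censored at the last contact. That censoring is caused by the endpoint itself, whereas the planned Kaplan-Meier, log-rank and Cox analyses assume that censoring carries no information about survival.

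Two things are at stake. The first is the absolute survival estimates, which the article's abstract offers as a benchmark for future research. The second is the primary pairwise comparison: if the chance of learning of a death differs between sites, part of that difference can pass into the treatment effect. Later analysis cannot recover deaths that were never ascertained.

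**Working it through.** **Inputs from the article.** Sample size: median OS 36 weeks (stenting), 27 (radiotherapy with or without chemotherapy), 14 (chemotherapy); 1102 stent patients, 464 + 212 = 676 radiotherapy patients; alpha 0.0167, taken as two-sided. Patient interviews: contacts at 1 and 3 months, then every 3 months. Study design: longest accrual 47 months, at least 6 months' follow-up.

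**Step 1: the plan's own power figure.** With exponential survival, HR = 27/36 = 0.75. Power = Φ(√(d·p₁·p₂)·|ln HR| − z), with p₁ = 1102/1778 = 0.620, p₂ = 0.380 and z = 2.393.
- d = 1210 events (14-month accrual plus 6 months): 16.89 × 0.2877 − 2.393 = 2.465, power 0.993.
- d = 1545 events (47-month accrual plus 6 months): 19.08 × 0.2877 − 2.393 = 3.096, power 0.999.

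The stated 0.99 reproduces, so power is not the weak point.

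**Step 2: equal under-ascertainment.** Assumption: a share m of deaths is never learned of, and each is censored at the last scheduled contact before death. Simulation used 400,000 exponential survival times per group, 47-month uniform accrual plus 6 months. It models missed deaths only, not living patients who drop out for unrelated reasons.

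| Missed deaths (m) | Stenting, true 36 | Radiotherapy, true 27 | Chemotherapy, true 14 |
|---|---|---|---|
| 10% | 39.7 | 29.6 | 15.3 |
| 20% | 44.1 | 32.7 | 16.7 |
| 30% | 49.7 | 36.9 | 18.7 |

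Cross-check: the observed hazard in the stent group is 0.908, 0.817 and 0.723 of the true hazard, and 36/0.908 = 39.6, 36/0.817 = 44.1, 36/0.723 = 49.8. The stent median is overstated by 10%, 23% and 38%.

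With 20% missed in both groups, the stent versus radiotherapy HR is 0.747 and power about 0.997.

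**Step 3: unequal under-ascertainment.** Also assumed. Rejection rates are from 1500 simulated log-rank tests of 1102 versus 676 patients at 0.0167.

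| Missed: stent / radiotherapy | HR when truth is 0.75 | Rejection when truth is 0.75 | HR when truth is 1.00 | Rejection when truth is 1.00 |
|---|---|---|---|---|
| 10% / 20% | 0.83 | 80% | 1.11 | 29% |
| 20% / 10% | 0.67 | 100% | 0.90 | 32% |
| 10% / 30% | 0.93 | 12% | 1.25 | 93% |
| 30% / 10% | 0.60 | 100% | 0.80 | 95% |

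With no missed deaths, or 20% in both groups, the same test rejects about 2% of the time under no true difference.

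**Step 4: could ascertainment differ by treatment?** In Table 1, ORCI has external beam radiotherapy and no stents. Tenwek, MNH and KCH have stents and no current radiotherapy (planned at KCH for 2022). KCMC has stents and refers radiotherapy to ORCI. Only MTRH lists both on site, with 320 of 2476 forecast patients (13%). Modality therefore largely follows site, although referrals from MNH and KCMC to ORCI blur this.

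**The case against.** The strongest case against runs as follows.

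- **Three attempts is a minimum.** A reader might infer that three failed calls end follow-up. The text does not say so: it sets a floor before classification, and nothing says chart abstraction stops when calls fail. What stands is that classification is permitted once the floor is met, and that follow-up runs only until loss.
- **Deaths enter by other routes.** The chart supplies date and cause of death, study teams work inside the clinics, and collecting cause of death at follow-up presupposes some informant, perhaps a relative who answers. This is fair. A reader might suppose that hospitals usually miss deaths at home, but the document has nothing on that. Still, no procedure secures an informant for a patient who is not reached or has no phone.
- **An article condenses.** Proxy numbers and tracing may be in the full protocol or site procedures. That would make the fix easier. However, the article states the contact rule down to the days of the week, and the point is about that rule.
- **Unequal bias is conjecture.** A reader might infer that the treatment comparison is certainly distorted. The document gives no loss rate, overall or by site, and four of the five stent sites are urban, with 472 + 253 + 320 + 93 = 1138 forecast patients against 862 at rural Tenwek, so modality does not divide by rural and urban. Centre-stratified tests and within-site analyses are planned. They help only where one site supplies both modalities.
- **Treatment-related mortality.** A reader might extend the point to this endpoint. The document does not support that: vital status and complications are recorded during treatment, and deaths close to treatment are the ones a hospital is most likely to know of.

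**Conclusion.** The concern holds as a risk built into the stated follow-up rule, not as a demonstrated bias. Unlearned deaths would be censored informatively, and absolute OS would be overstated. Under the assumptions of exponential survival and censoring at the last scheduled contact, the stent median would read about 40, 44 or 50 weeks instead of 36 if 10%, 20% or 30% of deaths were missed. The true share is unknown.

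The stent versus radiotherapy HR is nearly unaffected if ascertainment is equal. It is exposed if ascertainment differs by site, because modality largely follows site; a 10% versus 30% split would move 0.75 to about 0.93, and the reverse to about 0.60. The document neither states nor quantifies such a difference. The large sample gives no protection against it. This is a cheap improvement worth making while follow-up is running.

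**What to change.** 1. In Study design and Patient interviews, make 'not reached' a status for that interval only, and keep the patient on the 3-monthly schedule.
2. Before the June 2023 close, make one final vital-status check (patient, any recorded proxy, site records) for everyone not known to be dead. Assign 'lost to follow-up' only after that check, and report loss by treatment and by site.
3. For new enrolments, record a proxy number at the face-to-face interview, particularly for patients without a phone, and call it for vital status when the patient is not reached.

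The cost is extra calls by existing research assistants, an added form field and a consent line, which has to be introduced at six sites in three countries. Part 3 cannot reach patients already enrolled; for them the final check depends on the patient, site records and any proxy number already held.
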